## Methods/design

### Study design and setting

The IMPROVE trial is a 2 × 2 factorial feasibility RCT with a parallel process evaluation, i.e. the groups are not cross-over [35], conducted among pregnant women with an existing diagnosis of periodontitis. During recruitment, participants are allocated to one of four intervention arms using a permutated block randomisation matrix (Fig. 1). The arms are as follows:Semi-skimmed powdered milk fortified with additional sachet of 500 mg calcium and 500 IU vitamin D and early PT (PT during pregnancy)Semi-skimmed powdered milk fortified with additional sachet of 500 mg calcium and 500 IU vitamin D and late onset PT (PT after delivery)Semi-skimmed powdered milk with placebo sachet and early PTSemi-skimmed powdered milk with placebo sachet and late onset PT

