**Fig. 1 Fig1:**
[figure not shown]
SPIRIT flow diagram of the IMPROVE feasibility trial

The 2 × 2 design allows gathering evidence to feed into an adequately powered RCT to test two different hypotheses, so the four arms will enable estimation of the approximated effect that the specific combinations of the intervention components add to improving concentrations of maternal blood metabolic/inflammation markers and periodontal status.

Baseline data was collected up to second trimester (T0), with follow-up at third trimester (T1) and 6–8 weeks postpartum (T2).

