### Control group

The control group are the women assigned to the semi-skimmed powdered milk with non-fortified sachet (placebo) with similar colour, flavour, smell and texture as well as before and after dilution than fortified sachet, during pregnancy and late onset PT (after delivery). Late-onset PT starts after postpartum assessment, as part of the routine dental care in the prenatal clinic. This strategy is considered a more acceptable approach in comparison to offering no PT intervention, since the possibility of being assigned to an ‘untreated’ group could limit recruitment and is more ethical.

All participants were informed about the benefits of dairy food intake during pregnancy and given a brochure to take home with general information about healthy diet and oral health hygiene instructions once they entered the study.

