### Sample size

This is a feasibility study, and thus the final sample size will be determined by the number of participants that are feasible to recruit within the timescale and budget of the project. For feasibility studies, a minimum of 12 subjects per group is proposed by Julious [54], and a total sample size of 70 subjects is proposed by Teare et al. [55] for a continuous outcome. Since we are planning a 2 × 2 factorial RCT, a sample size of 120 (30 per group), would be enough to detect a realistic event and allowing for 58% dropout rates (considering a sample size of 70), with sufficient precision and minimal bias for the estimates, as well as the existence of an additive interaction between the two interventions.

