### Statistical analysis

Baseline characteristics of participants will be summarised using descriptive statistics (i.e. means and standard deviations for normally distributed continuous variables, medians and ranges for skewed continuous variables, frequencies and proportions for categorical/binary variables), for all four intervention arms and total sample. All analyses will be according to the intention-to-treat approach, including all participants, regardless of adherence to the study protocol. To determine the effects of the intervention, time and group-time interaction on outcomes (inflammatory biomarker concentrations and periodontitis status), one-way repeated measures ANOVA will be used. Intervention will be regarded as a between-subject factor and time with three-time points (T0, T1 and T2) as a within-subject factor. Mean change of biomarker concentrations, number of sites with bleeding on probing and clinical attachment level (periodontal status) will be compared between the four treatment groups using ANCOVA, adjusted for their baseline values. A *P* value < 0.05 will be considered statiscally significant.

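### The 2 × 2 factorial trial is analysed as one four-group factor, so the stated tests do not separate the fortification effect, the PT-timing effect and their interaction

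*Protocol article*

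**What the plan says.** Under Study design and setting, the protocol article calls the trial a "2 × 2 factorial feasibility RCT with a parallel process evaluation", with sachet (fortified or placebo) crossed with PT timing (early or late). The text after Fig. 1 gives two reasons for the design. It "allows gathering evidence to feed into an adequately powered RCT to test two different hypotheses", and the four arms are to permit "estimation of the approximated effect that the specific combinations of the intervention components add".

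Table 1 lists, as secondary objectives, effect sizes and variability for sizing a definitive RCT, and initial effects on biomarkers and periodontitis status. The Sample size section plans 120 women, 30 per group, and appeals among other things to an additive interaction between the two interventions.

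The Statistical analysis section names two models. For the repeated measurements, "one-way repeated measures ANOVA will be used", with intervention as the between-subject factor and time (T0, T1, T2) as the within-subject factor. Mean changes "will be compared between the four treatment groups using ANCOVA, adjusted for their baseline values". No sachet effect, PT effect, sachet × PT term or contrast is named. The only interaction mentioned is group by time.

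**The concern.** The design has two randomised factors, and the analysis has one factor with four levels. A significant four-group result says that the cells differ somewhere. It does not say whether fortification, PT timing or their combination is responsible. Someone planning the definitive RCT needs an estimate and a confidence interval for each component, plus some idea of the interaction, and the stated analysis does not commit to reporting any of these. If the contrasts are chosen only after the four-group result is known, the choice can depend on the data. If the follow-up is cell against cell, each comparison uses about 30 women per side where a factorial contrast uses about 60.

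**Working it through.** **Inputs.** From the protocol: four arms, 30 women per arm, N = 120, and significance at P < 0.05 (two-sided assumed). The Sample size section also mentions a sample of 70, used here as a second, smaller N (17.5 per cell on average). The protocol states no SD and no effect size, so everything below is in SD units, effects are assumed, and any gain from baseline adjustment is ignored.

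**Protocol figure.** 4 × 30 = 120 reproduces. Each level of each factor holds 2 × 30 = 60 women before dropout.

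**What the four-group test contains.** Four cells give 3 df: 1 for sachet, 1 for PT timing, 1 for sachet × PT. A simulated data set with 30 per cell confirms the split: the four-group sum of squares is 7.443, equal to 7.332 + 0.096 + 0.015 for sachet, PT and interaction, with the same residual in both fits. With three time points, group by time has 3 × 2 = 6 df and splits the same way into three parts of 2 df.

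**Precision from the same four cell means, n per cell.**
- Marginal effect (weights ½, ½, −½, −½): SE = √(1/n).
- One cell against another: SE = √(2/n).
- Interaction, as a difference of differences: SE = √(4/n).

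| Contrast | SE, N = 120 | SE, N = 70 | 95% CI half-width, N = 120 (1.96 × SE) |
|---|---|---|---|
| Marginal effect | 0.183 | 0.239 | 0.36 |
| Cell vs cell | 0.258 | 0.338 | 0.51 |
| Interaction | 0.365 | 0.478 | 0.72 |

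The cell-vs-cell SE is √2 = 1.41 times the marginal SE. The marginal SE is the same whether it comes from a two-factor fit or as a contrast of the four-group fit.

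**Power, for illustration.** Noncentral F with N − 4 error df. For a main effect d in one factor and no interaction, the noncentrality is N·d²/4 for both tests; with N = 120 and d = 0.5 it is 120 × 0.25/4 = 7.5.

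| Assumed d | 1-df, N = 120 | Four-group, N = 120 | 1-df, N = 70 | Four-group, N = 70 |
|---|---|---|---|---|
| 0.3 | 37% | 24% | 24% | 15% |
| 0.5 | 78% | 61% | 54% | 37% |
| 0.7 | 97% | 90% | 82% | 66% |

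**The opposite case.** Suppose 0.5 SD appears only in the combined cell. Each marginal effect is then 0.25 SD, with noncentrality 120 × 0.25²/4 = 1.875. For the four-group test it is 30 × 0.5² × ¾ = 5.625. At N = 120 the power is 27% for each 1-df main effect and 48% for the four-group test; at N = 70 it is 18% and 28%. The ranking reverses.

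**The case against.** The strongest reply is that a baseline-adjusted ANCOVA on four groups is the saturated 2 × 2 model. Both marginal effects and the interaction are contrasts of that fit, with the standard errors shown above. A reader might infer that the 60-vs-60 comparison is lost or that the component estimates cannot be produced. The documents do not support that: the data and the fitted cell means contain them. What remains is that the stated comparison is of four groups and no factor contrast is specified.

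The design text also asks about specific combinations, and a four-cell display serves that purpose. This stands, and it is why the cell means belong in the report. It does not replace the two factor contrasts, which the same text motivates by speaking of two hypotheses.

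Efficacy is secondary in a feasibility trial, and the protocol leaves formal testing to a later RCT. It would therefore be wrong to read the power figures as a confirmatory failure. Nor do they show that the factorial test is always better, as the combined-cell case proves.

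Two further readings carry little weight. The label one-way is loose, but the next sentence of the protocol makes the intended between-within structure clear. The Control group section treats the placebo, late-PT cell as the control, but it describes what those women receive. It prescribes no cell-against-cell analysis, and neither does the Statistical analysis section.

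**Conclusion.** The point holds as a mismatch between the stated analysis and the design. The four-group test pools two main effects and an interaction. It does not deliver the per-component estimates needed for planning, or the interaction that the Sample size section invokes. The consequence is limited: nothing is lost from the data, and only secondary outcomes are affected.

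The firm number is precision, which follows from the allocation alone: 0.183 SD for a marginal effect against 0.258 SD for a cell pair at N = 120. The power difference (17 points at 0.5 SD, 78% against 61%) rests on an assumed effect and on no interaction. The interaction is imprecise under any analysis (SE 0.365 SD at N = 120), so its confidence interval is informative but a test of it is not something to rely on.

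**What to change.** In both the baseline-adjusted ANCOVA and the repeated-measures model, replace the single intervention factor with fortification (yes/no), PT timing (early/late) and fortification × PT timing. In the repeated-measures model, cross each of these with time. Report the two marginal effects (about 60 vs 60 before dropout) and the interaction contrast, each with a 95% CI. Show the four cell means alongside, because the protocol asks about specific combinations and a marginal effect can mislead when there is an interaction. Call the repeated-measures model mixed (between-within), not one-way.

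The cost is a change of wording before analysis. Recruitment, data collection and treatment are untouched. The one drawback is that marginal effects average over the other factor, which showing the cell means addresses.

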### Objectives

The primary and secondary objectives are described in Table 1.

**Table 1 Tab1:** Objectives of the IMPROVE feasibility trial

Primary	Secondary
1. Feasibility of recruitment strategy for local health service and participants	1. Estimates of effect size and variability to enable accurate sample size and power calculations for a definitive RCT
2. Time necessary to recruit participants	2. Identification of any differences across age groups and other socio-demographic factors with regards to attrition rate
3. Acceptability of the study design and random allocation	3. Identification of key barriers and enablers to adoption, and large-scale implementation, of the IMPROVE trial are
4. What the most appropriate inclusion/exclusion criteria are	4. Definition of required for economic analysis and if they can be collected reliably
5. Estimates of compliance, satisfaction, follow- up and attrition rates	5. The capacity of the research team to embed this study into routine practice in the Public Health Centres
	6. To determine the initial effects of the intervention, time and intervention-time interaction on inflammatory biomarkers concentrations and periodontitis status

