### Dental examination

After initial screening, participants underwent a full periodontal examination at baseline (T0) and postpartum (T2). Periodontal examination was performed in full mouth at six sites per tooth (known as mesiobuccal, mid-buccal, distobuccal, mesiolingual, mid-lingual and distolingual), using North Carolina periodontal probes, dental mirror and gauze, but without X-rays. The model chosen is justified because no partial record model presents reliability to replace full mouth examination [49]. The T0 and T2 evaluations take place in the recruitment room, using a simple chair and a forehead flashlight. Maintenance examinations are performed to assess the periodontal status of those who had finished the treatment during pregnancy, and these examinations are done every 2 months. Data collection included gingival bleeding on probing, probing depth, cementoenamel junction-gingival margin distance (CAL) and dental mobility. A tailored form was developed to register the data. Oral examination and treatment procedures were performed by calibrated and trained dentists. The dentists always calibrated their probing force using a scale right before the clinical examination. The recommended probing force was approximately 20 g of pressure [50].

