#### Secondary outcome measures

Changes in mean and SD of percentage of sites with bleeding on probing (BOP) and CAL between postpartum and baselineChanges in maternal blood levels of biomarkers of inflammation (CRP, IL-6 and MMP-9)Changes in maternal blood levels of 25(OH) D, glucose, insulin, calcium, parathyroid hormone and lipids (HDL, LDL and triglycerides)Neonatal blood levels of 25(OH) D and calcium

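### An unqualified P < 0.05 rule is fixed for the secondary efficacy outcomes of a feasibility trial, with two unranked analyses for five of them

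*Protocol article*

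**What the plan says.** All from the protocol article.

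- **Outcome measures.** The primary outcomes are feasibility, recruitment, adherence and attrition. The secondary outcomes are two periodontal measures (bleeding on probing, BOP; clinical attachment loss, CAL), three inflammatory markers (CRP, IL-6, MMP-9), eight further maternal blood measures ("Changes in maternal blood levels of 25(OH) D, glucose, insulin, calcium, parathyroid hormone and lipids (HDL, LDL and triglycerides") and two neonatal ones ("Neonatal blood levels of 25(OH) D and calcium").
- **Statistical analysis, first method.** The section gives this method as follows: "To determine the effects of the intervention, time and group-time interaction on outcomes (inflammatory biomarker concentrations and periodontitis status), one-way repeated measures ANOVA will be" applied. The model is further described as having "time with three-time points (T0, T1 and T2) as a within-subject factor".
- **Statistical analysis, second method.** Mean changes in biomarkers, bleeding sites and attachment level "will be compared between the four treatment groups using ANCOVA, adjusted for their baseline values".
- **Statistical analysis, decision rule.** "A *P* value < 0.05 will be considered statiscally significant".
- **Objectives, Table 1.** Secondary objective 1 asks for effect sizes and variability with which to plan a definitive trial. Secondary objective 6 reads "To determine the initial effects of the intervention, time and intervention-time interaction on inflammatory biomarkers concentrations and periodontitis status".
- **Study design and setting.** The factorial design is meant to gather evidence for a later, adequately powered trial, which would test the two hypotheses.
- **Dental examination.** "participants underwent a full periodontal examination at baseline (T0) and postpartum (T2").

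**The concern.** The 5% threshold applies to the only tests described, and none of those bears on a primary outcome. For the inflammatory and periodontal outcomes the article sets out two analyses of the same question: do the groups differ in how the outcome changes? It does not say which one supplies the result. If the group-time interaction gives P = 0.03 and the ANCOVA gives P = 0.12 for the same marker, the text as written lets that marker be called significant.

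At stake is how the results are read. Secondary objective 1 needs an estimate and its uncertainty for each outcome. A significance label, given without caveat by a trial that states no power for these outcomes, invites a reader to treat a chance result as a signal of benefit when the definitive trial is planned.

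**Working it through.** The article gives no family-wise error rate and no power for these outcomes, so there is no figure of that kind to reproduce. Its only error-rate figure is 0.05 per test.

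**1. Which outcomes fall under which analysis**

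- Both analyses: CRP, IL-6, MMP-9, BOP and CAL, since the ANOVA is named only for inflammatory biomarkers and periodontitis status. That is 3 + 2 = 5.
- ANCOVA only, reading its reference to biomarkers broadly: 25(OH)D, glucose, insulin, calcium, parathyroid hormone, HDL, LDL and triglycerides. That is 8, and 5 + 8 = 13 maternal outcomes.
- Neither: the two neonatal measures, which have no baseline and no repeats.
- BOP and CAL have full examinations at T0 and T2 only, so their group-time test rests on two time points although the ANOVA is specified with three.

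**2. One test per outcome, independent outcomes**

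P(at least one P < 0.05) = 1 − 0.95^k.

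- k = 5: 1 − 0.95^5 = 22.6%
- k = 13: 1 − 0.95^13 = 48.7%

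**3. Either test may count: simulation under no effect**

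From the article: four arms of 30, alpha 0.05, and the outcome sets in step 1. Assumed: normal data, no dropout, correlation 0.5 between visits within a woman, and between-outcome correlation of 0.8, 0.5 or 0. The tests are the four-group ANCOVA at T2 (3 degrees of freedom) and the group-time interaction. The ANOVA's overall intervention effect is not counted; counting it could only raise the rates.

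For a single outcome, the chance that at least one of the two tests gives P < 0.05 is about 7-9%. It is near 7% with two time points and near 8.5% with three.

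| Counted as a false positive | corr. 0.8 | corr. 0.5 | corr. 0 |
|---|---|---|---|
| Five outcomes, ANCOVA only | 14% | 19% | 22% |
| Five outcomes, either test | 22% | 28% | 34% |
| Thirteen outcomes, ANCOVA only | 22% | 35% | 49% |
| Either test for five, ANCOVA for the other eight | 28% | 41% | 56% |

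Repeat runs put the central either-test values at 27-30% (five outcomes) and 41-44% (thirteen). With 17 women per arm, close to the 70 in the Sample size section, the ranges barely move: 22-34% and 27-56%.

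**4. Hand check of the independent column**

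- Five outcomes: 1 − 0.915^3 × 0.93^2 = 1 − 0.766 × 0.865 = 34%
- Thirteen outcomes: 1 − 0.766 × 0.865 × 0.95^8 = 1 − 0.663 × 0.663 = 56%

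**5. The rule beside the aims**

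Secondary objective 1 calls for estimates. Study design and setting leaves the hypotheses to a later powered trial. Statistical analysis fixes a significance verdict and does not mention confidence intervals.

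**The case against.** The best reply is that the article already frames the trial as non-confirmatory. Feasibility is primary, every clinical outcome is secondary, objective 6 speaks of initial effects, and no decision hangs on P < 0.05. Multiplicity rules and the choice of lead model are commonly left to an analysis plan, which is not shown here.

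Much of this stands. The absence of a multiplicity rule is not held against the article. The point rests on what the article does state: a threshold without qualification, and two analyses without an order. The framing is also less consistent than the reply suggests. Statistical analysis drops the word initial, and Sample size says 120 women suffice to detect a realistic event and an additive interaction, yet gives no effect size, standard deviation or power.

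A reader might infer several stronger things that the documents do not support:

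- *That all secondary outcomes are tested twice.* The ANOVA is named for five only, and the neonatal measures fit neither model.
- *That a false positive is more likely than not.* In the central setting the rate is 28% for five outcomes and 41% for thirteen. It passes one half only for thirteen outcomes with correlation near zero.
- *That a promised error rate is broken.* The 5% is a per-test threshold, and the rates above are family-wise.
- *That the plan makes an efficacy claim.* A chance P < 0.05 is not one, and no passage chooses the definitive trial's outcome by P value.

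The thirteen-outcome figure also assumes no effect on 25(OH)D, calcium and parathyroid hormone, which the supplement could be expected to move. The five-outcome figure is the safer one to quote.

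**Conclusion.** The concern holds in limited form. The Statistical analysis section attaches an unqualified 5% significance rule to secondary efficacy outcomes and leaves two analyses unranked for five of them. With either test allowed to count, the false-positive rate under no effect is about 7-9% for one outcome and about 28% (22-34%) for at least one of five. It is about 41% (28-56%) when one ANCOVA for each of the other eight maternal outcomes is added. The figures rest on the assumed correlations, normal data and no dropout, and on the text permitting either test to count, which it neither states nor rules out. The rule serves neither the stated need for effect estimates nor the stated plan to test hypotheses later. This merits a wording correction; it does not undermine the design.

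**What to change.** In Statistical analysis, replace the significance sentence with text such as: *Comparisons of secondary outcomes are exploratory. They will be reported as estimated differences with 95% confidence intervals, without declarations of statistical significance, and no conclusion about efficacy will be drawn from them.* Then name the baseline-adjusted ANCOVA as the single source of the effect estimate for each outcome it covers, and describe the repeated-measures time and interaction results as supportive.

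This needs no new data and no extra participants. The small cost is that the team gives up unadjusted claims of significance on secondary outcomes, which a feasibility trial does not need.

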### Data management

Questionnaires (quantitative data) are performed directly using RedCap software (Research Electronic Data Capture), with features that minimises data entry errors and facilitates conversion to other statistical software for data analysis. Questionnaires were designed specifically so that data entry in RedCap was made as accurate as possible.

Questionnaires are peer reviewed before data entry to search for missing data, erroneous values and inconsistency*.* The identified problems are being solved (data cleaning) using Stata 12 software (Stata Corp 12, TX, USA). Quantitative data are being held in Stata data file (.dta), which has the capacity to store hundreds of variables. Stata software is widely used in research and files can be easily converted into other formats via Stata transfer software. Qualitative interviews are being audio recorded (with full participant consent) and stored in MP3 files. Transcripts are analysed by thematic content analysis and Nvivo software for supporting qualitative analysis is used.

All laboratory specimens, evaluation forms, reports, and other records are identified in a manner designed to maintain participant confidentiality. All records are kept in secure cabinets with limited access. Clinical information cannot be released without the written permission of the participant, except as necessary for monitoring and auditing by the sponsor and regularity authorities. The investigator and the study site staff involved in this study are not allowed to disclose or use for any purpose other than performance of the study.

Computers used to collate the data have limited access measures via user names and passwords. Published results will not contain any personal data that could allow the identification of individual participants. All confidential data (name, address, etc.) are archived separately from research data. Data are housed on a secure server protected by university firewalls and are subject to backups.

